### Sample size calculation

The sample size was calculated using G*Power 3.1.9.2 [65]. Earlier results obtained on NET with children [5, 31] suggest large between-groups effect sizes of *d =* 0.7–1.0 for PTSD symptom severity for NET vs. waiting list. For determining the effectiveness of NET vs. waiting list, with α = 0.05, *d =* 0.85 (*f ≈ 0.40)* and a priori test power = 0.80 (β = 0.20), 52 participants would be required for analyses of covariance of fixed effects, main effects and interactions on primary outcomes.

There are no effect size estimations available for TAU as offered to traumatized children at participating clinics, nor could such estimations be reliably made, taking into account the diverse nature of TAU expected. However, at least some effectiveness for TAU over a waiting list can be assumed. Thus, in order to tease out differences in NET vs. TAU between-treatments comparisons, we needed to aim for a sample size that is somewhat larger than that required for detecting NET vs. waiting list between-groups differences. At the same time, dropout rates for participation in NET reported in earlier studies are generally very low [29, 66], so little attrition is expected. In light of these considerations and practical limitations, we aim for a sample of 80 participants.

### Randomization

To continuously provide close to equal numbers of participants in the control and treatment groups for interim analysis, random allocation is performed using a randomized block design with variable block sizes and an allocation ratio of 1:1 [67].

At the start of the study, before any participants were recruited, the participating clinics were provided with folders by the research group, each containing all the relevant research material, questionnaires and measurements for one participant. A sealed envelope was placed by the research team in each folder with a piece of paper inside. Half of these papers were marked “NET” and the other half “TAU”. Whenever a suitable participant is identified at a study location by a clinician and informed consent is received from her/him and her/his parents or guardians, the clinician will randomly select a folder for her/him. The envelope will then be opened and its content will determine whether the participant receives NET or TAU. Allocation was concealed by the use of opaque, sealed envelopes.

Due to most participating clinicians acting both as treatment providers and assessors, blinding them as to the treatment status of each participant beyond randomization (after T0) is not possible and will not be attempted. The participants themselves cannot be blinded to the intervention, as the differences between TAU and NET will make it obvious to them which group they belong to.

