There are two control conditions. First, the time each child spends waiting for treatment to begin, typically three months, will be considered a waiting list control condition. Second, each participant will be randomized into one of two groups. One group will receive NET, acting as the study group, and the other group, receiving TAU, will act as a positive-control group. The trial is parallel-group in nature, with a randomized block design with varying block sizes and an allocation ratio of 1:1.

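### The allocation procedure lets the enrolling clinician pick any folder, which does not match the stated variable-block design and leaves no fixed next allocation

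*Protocol article*

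**What the plan says.** The Trial design section describes a parallel-group trial "with a randomized block design with varying block sizes and an allocation ratio of 1:1". The Randomization section repeats this ("random allocation is performed using a randomized block design with variable block sizes and an allocation ratio of 1:1") and gives the reason: "To continuously provide close to equal numbers of participants in the control and treatment groups for interim analysis".

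The same section then sets out the mechanics. Before recruitment began, "the participating clinics were provided with folders by the research group", one folder per child, each holding a sealed envelope. Half the envelopes contain a NET slip and half a TAU slip. Once consent is obtained, "the clinician will randomly select a folder for her/him"; the envelope is opened and "its content will determine whether the participant receives NET or TAU". The safeguard stated is: "Allocation was concealed by the use of opaque, sealed envelopes".

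Three other statements bear on this. The Procedure section says the treating clinician will in most cases also be the assessor, and places the T0 assessment before assignment. The Randomization section says clinicians will not be blinded after T0. The Ethical issues section schedules an interim comparison of NET and TAU on the first 20 participants, which can stop the trial.

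**The concern.** A block design works by fixing the order of allocations. If the person enrolling may take any folder from the stock, whatever order the research group prepared has no effect. The named design and the described mechanism therefore disagree, and the balance that blocking was chosen to deliver is not assured.

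The second issue is concealment. An opaque envelope stops a clinician from reading an allocation before opening it. It does not settle which envelope must be opened. Without a designated next folder, using a different one is not visibly out of sequence. The clinician choosing is usually also the child's therapist and the person who collects the outcomes, unblinded.

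NET versus TAU is the only randomised contrast, because the waiting-list comparison uses each child's own time before treatment. If allocation were steered, covariance adjustment for age, gender and treating unit could not correct for the unrecorded reasons behind it.

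**Working it through.** The article gives no figure to reproduce. The check has three parts.

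**1. Design against mechanism.** Permuted blocks need an ordered list, used in order. The described step is a draw without replacement from a balanced stock with no stated order. A complete random draw from a balanced set has the same distribution as one permuted block, so a clinic's whole stock can be read as a single block. The article does not say this and does not give the stock size.

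**2. Balance at the interim.**

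Inputs from the article: a target of 80 (40 per arm), five named units, and an interim on the first 20 children. Assumptions not in the article: the stock per unit, four children from each of five units at the interim, no children from private practitioners, and the first 20 assessed being the first 20 randomised.

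For a stock of M folders, half of them NET, with n drawn, the number X of NET allocations follows

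P(X = k) = C(M/2, k) · C(M/2, n − k) / C(M, n).

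A 13:7 or worse split means that total NET differs from 10 by at least 3. With several units, the unit distributions are convolved.

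| Assumed stock | Folders in total | P(13:7 or worse) |
|---|---|---|
| 2/2 in each of 5 units | 5 × 4 = 20 | 0% |
| 3/3 | 5 × 6 = 30 | 7% |
| 4/4 | 5 × 8 = 40 | 13% |
| 5/5 | 5 × 10 = 50 | 17% |
| 8/8 | 5 × 16 = 80 | 21% |
| One pool of 40/40 | 80 | 19.6% |

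Worked example for 3/3: in one unit, P(1 NET of 4) = C(3,1)·C(3,3)/C(6,4) = 3/15 = 0.2, P(2) = 9/15 = 0.6 and P(3) = 0.2. Each unit is thus one below, level or one above with probabilities 0.2, 0.6, 0.2. A net shift of at least 3 over five units has probability

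2 × [(10 × 0.2³ × 0.6² + 5 × 0.2⁵) + 5 × 0.2⁴ × 0.6 + 0.2⁵] = 2 × [0.0304 + 0.0048 + 0.0003] = 0.071.

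The smaller stocks would need resupply to reach 80 children; the article neither mentions nor excludes this. The single pool is a reference case only, because the folders are held at separate clinics.

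Benchmark: permuted blocks of 2, 4 or 6, equally likely, within each unit. For the first four children of a unit, P(1 NET) = 1/3 × 1/5 + 1/3 × (1/3 × 1/6 + 1/3 × 1/5) = 0.067 + 0.041 = 0.107, the same for 3 NET, and 0.785 for 2 NET. The same sum over five units gives about 1.6%.

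Cost of imbalance: relative efficiency at 13:7 is 4 × 13 × 7 / 20² = 364/400 = 91%, a loss of 9%.

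**3. Predictability.** Suppose an unblinded clinician always guesses the arm that is behind in the unit, with ties counted as half right. By simulation over 16 allocations, the guess is right 63% of the time with an 8/8 stock and about 70% with 2/4/6 blocks. Over the first four allocations the figures are 53% and 67%. Small blocks improve balance and make the next allocation easier to guess.

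**The case against.** Several points on the other side have force.

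- If each clinic's set is balanced, it is a block, and sets of different size are blocks of varying size. The text does not exclude this, so it would be too strong to say that there is no blocking. How sets were composed, numbered or logged may be in the full protocol. This stands in part. It does not remove the conflict: the article positively describes a free choice of folder, and one large block per clinic does not ensure arms that are close to equal at every point.
- The imbalance depends on a stock size that is not stated, can be nil, and costs little even at 13:7. This stands. A reader might infer that the stated aim of balance fails outright. The article does not support that, because it gives no stock size and does not define close to equal; even with 8/8 stocks about 79% of interims would be at 12:8 or better.
- A reader might infer that an unwanted envelope can be swapped without trace. That goes too far. An opened envelope has a broken seal, and a discarded single-child folder leaves a shortfall against the number supplied. Unopened folders are not described as distinguishable, so choosing among them reveals nothing about the arm. Consent precedes selection, T0 precedes assignment, and baseline group comparisons are planned. These safeguards reduce the risk. But the article describes no reconciliation of folders, and baseline comparisons may not show selection on unmeasured factors.
- Predictability as a stock runs down is not an argument for small blocks, which are easier to guess. This stands, and it limits the choice of remedy.

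**Conclusion.** The point holds in limited form. The stated variable-block design and the described procedure do not agree, and the procedure leaves the choice of folder to a clinician who is usually also the unblinded therapist and assessor. Nothing designates the next folder, so a departure would be hard to detect, though not impossible.

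A reader might go on to conclude that concealment was broken or that allocation was steered. The article shows neither, and any resulting bias cannot be estimated from it.

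The effect on balance is secondary. The chance of 13:7 or worse at the interim is between 0% and about 21% under the stock sizes assumed, against about 1.6% with 2/4/6 blocks within unit, and the efficiency loss at 13:7 is about 9%. These probabilities rest on five units with four children each; the single 40/40 pool gives 19.6%.

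This should be fixed. It does not by itself undermine the trial.

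**What to change.** For the folders not yet used:

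- Number them consecutively within each unit, and fill them from a permuted-block list with variable block sizes, generated by someone who does not enrol children.
- Keep the block sizes undisclosed and not all very small. Very small blocks within a unit balance well but are easier for unblinded clinicians to guess.
- Require the lowest-numbered unopened folder to be used, with the child's study ID and the date written on the envelope before it is opened.
- Keep a log of opened envelopes and reconcile it against the number of folders supplied.

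In the text, make the Trial design and Randomization sections describe one and the same method, and report how the children already enrolled were allocated, including the size of each unit's stock and any resupply.

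The Trial status section says enrolment is continuing, so the change is still possible. It costs a short amendment, relabelling and refilling of the remaining folders, and a simple log. It needs no additional children or staff.

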All clinicians providing treatment will receive a three-day training on NET by instructors experienced in the method. Each participating unit will be provided with NET manuals. For the NET intervention group, clinicians are instructed to adhere as strictly as possible to the intervention as laid out in the NET manual. Semi-annual supervisory meetings will be organized with the clinicians and the research team to discuss the use of the treatment method and any issues in implementing it that may have appeared. The developers of the method are also available for supervisory purposes via Skype.

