### Procedure

A sequential procedure will be applied to data collection. Whenever a child is identified as a potential participant by a clinician at one of the co-operating units, information concerning the intervention and the related research is provided both to the participant him/herself and to his/her parents. If they are willing to participate in the research, informed consent will be requested from the child and his/her parents.

Waiting list control baseline data (T0) will be collected during this first meeting with the clinician. The children will then be randomly assigned to EITHER the ‘treatment as usual’ group (n = 40) OR the ‘NET intervention’ group (n = 40). Because of the treatment queues currently present at most of the treatment units, all participants will first be placed under waiting-list conditions for approximately three months (waiting list control condition, n = 80). In the unlikely case that there is no treatment queue at the moment, the participant will begin NET or TAU immediately and will not contribute waiting list control data.

At the start of the intervention or TAU, pre-test (T1) data will be collected from all participants. The T1 data will serve as an end measurement for the waiting list control condition and as the pre-test measurement for the NET intervention and the TAU control condition.

Data (T2) will also be collected once during the treatment for both the NET and the TAU groups. This will allow for proper analysis of mediating mechanisms. In the NET group, this assessment will take place at the time when the worst traumatic memories have been narrated.

Post-test data (T3) will be collected from participants in both groups, immediately after the intervention for the NET group, and after three months of treatment for the TAU group, and follow-up data (T4) will be collected during a joint family meeting, three months later.

In most cases, the clinician working as the therapist will also act as the assessor and collect data from the patients he/she is treating. In some cases, members of the research team may carry out some assessments, particularly for follow-up. Interpreters are used whenever needed during assessments, and will be present during all assessment and treatment sessions for children who are not fluent in Finnish.

The procedure will be continued until the sample size reaches the goal of n = 80, with data collection estimated to finish during 2017.

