Due to restrictions on the use of the tests used for measurements of cognitive performance, these additional assessments will be carried out by a member of the research team (SK), a licensed clinical psychologist, and studied in a smaller subsample. For n = 20 participating children about to start treatment during 2015, willingness and informed consent to participate in these additional tests will be requested, and the measurements will then be carried out at T0 and T4 for this subsample.

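### The reason given for not blinding covers treating clinicians only; the protocol could cheaply mask the research-team examiner of the cognitive tests, on whom it is silent

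*Protocol article*

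**What the plan says.** The Randomization section of the protocol article is the only place that deals with blinding after allocation, and it makes two statements. The first concerns clinicians and opens with its ground: "Due to most participating clinicians acting both as treatment providers and assessors, blinding them as to the treatment status of each participant". The conclusion drawn there is that such blinding, once the child has been allocated, cannot be done and is not planned. The second concerns children: "The participants themselves cannot be blinded to the intervention".

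The Procedure section gives the cognitive tests to someone else. Because use of the tests is restricted, "these additional assessments will be carried out by a member of the research team", a licensed psychologist. The subsample is described thus: "For n = 20 participating children about to start treatment during 2015", and "the measurements will then be carried out at T0 and T4 for this subsample". The same section says that "members of the research team may carry out some assessments, particularly for follow-up".

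The sections Primary outcomes and Effect evaluation both list cognitive performance as a primary outcome. The section on the NET intervention adds a point of contact between the team and the therapists: "Semi-annual supervisory meetings will be organized with the clinicians and the research team".

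**The concern.** The protocol accepts unblinded assessment for a reason that is sound for most of its data: a therapist who assesses his or her own patient cannot be blind. That reason does not carry over to an examiner who does not treat the child, and nothing in the article keeps this examiner unaware of the arm.

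The other primary outcomes (PTSD symptoms, depressive symptoms, distress, resilience) are questionnaires answered by a child who knows the treatment, or by a parent or guardian on one SDQ form, and mostly collected by the therapist. The cognitive tests already have a separate examiner, so they are the one primary outcome for which assessor masking is within reach of the planned staffing. Individually given tests leave some room for encouragement, timing and scoring to follow the examiner's expectation. If the examiner knows the arm, a NET-TAU difference on these tests is open to that explanation, and nothing recorded in the trial could rule it out.

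**Working it through.** No figure in the protocol bears on this point. Its one computed figure, 52 participants, does reproduce (ANCOVA F test, numerator df 1, f = 0.40, α = 0.05, power 0.807), but masking an examiner changes neither sample size nor power. The check is therefore mainly a comparison of statements.

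**1. Whom the blinding statement covers.** The object of the sentence in Randomization is the participating clinicians, and the ground is their double role. Participants are dealt with separately. Non-treating assessors appear in neither statement.

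**2. Who measures what.**
- CRIES, DSRS, CYRM and the child SDQ: child self-report, collected in most cases by the treating clinician (Procedure).
- WMTB-C, RPM and TMT: performance tests, given by a research-team member who is not described as treating the children (Procedure).
- Some other assessments, mainly at follow-up: possibly research-team members (Procedure).

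The double-role ground covers the first group and does not reach the other two.

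**3. How a non-treating assessor could learn the arm.**
- Supervisory meetings bring the research team and the clinicians together twice a year to discuss how the method is being used (NET intervention).
- Children know their arm (Randomization) and can mention it.
- T4 data are collected at a joint family meeting (Procedure), where treatment is a natural topic.

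These make disclosure plausible. They do not show how often it will happen.

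**4. Whether T0 is also exposed.** Under Procedure, T0 data are collected at the first meeting with the clinician and the child is then randomized. The cognitive tests need a separate request and a different examiner, and they are offered to children about to start treatment. A cognitive T0 test could therefore fall after the envelope is opened. The article does not settle this.

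**5. Scale.** The split of the 20 children is not stated; 10 per arm is assumed from the 1:1 allocation. In units of the outcome SD, the unadjusted standard error of a NET-TAU difference is

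√(1/10 + 1/10) = √0.2 = 0.447.

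The documents give no size for examiner bias. Assuming 0.2 to 0.4 SD:

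- 0.2 / 0.447 = 0.45 of a standard error
- 0.4 / 0.447 = 0.89 of a standard error

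An uneven split changes little. With 12 and 8, the standard error is √(1/12 + 1/8) = 0.456, and the ratios are 0.44 and 0.88. Covariate adjustment that shrinks the standard error would raise the ratios.

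For context, at 10 per arm power is about 0.19 for d = 0.5 and 0.44 for d = 0.85, and the effect detectable with 80% power is about d = 1.32. Random error is thus the larger problem in this subsample, and a bias of the assumed size could not be recognised in the data.

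**The case against.** The strongest reply is that the protocol says nothing wrong. A reader might infer that it rules out blinding for everyone, the cognitive examiner included. The text does not support that: it declines blinding for clinicians, notes that participants cannot be blinded, and leaves other assessors unmentioned. This is an unused safeguard, not a contradiction. The article also condenses a fuller protocol that is not shown, in which masking of this examiner may be described. That stands as a caution, but the article does take up blinding and treats clinicians and participants in turn, so the gap is worth closing.

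A reader might also infer that the examiner will usually know the arm, because the research team filled the envelopes, attends supervisory meetings and may run the interim comparison. None of this shows it. The envelopes are opaque and sealed, and a clinician picks the folder, so preparing them does not reveal a given child's arm. No section says that this examiner attends the meetings or that individual children are identified there. The Ethical issues section does not say who runs the interim analysis, and a group comparison need not reveal any one child's allocation.

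It is also fair to say that performance tests are less open to assessor influence than interviews or ratings, that masking would be incomplete, and that the bias range is assumed. All of this stands and limits the weight of the point. It does not remove it: the stated reason for not blinding does not apply to these assessors, and nothing else in the article protects their measurements.

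**Conclusion.** The point holds as a cheap improvement of limited reach. For one named primary outcome, and for any follow-up data collected by the research team, the article neither keeps the assessor unaware of the arm nor gives a reason why it could not. Such an assessor may well learn the allocation; that this will usually happen is not established.

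The benefit covers 20 of up to 80 children (20/80 = 25%) and an unstated amount of other follow-up data. It would be wrong to expect it to make the primary outcomes as a whole free of expectation: CRIES, DSRS, SDQ and CYRM are reports by unblinded respondents and gain nothing from masking this examiner. The figure of 0.45 to 0.89 of a standard error rests on an even split, an unadjusted comparison and an assumed bias of 0.2 to 0.4 SD. It shows scale only and is not an estimate of actual bias. Nor is the change free, since masking needs a procedure and will sometimes fail.

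**What to change.** The sentence on clinicians can stay, since it already concerns them alone. Add to the Randomization or Procedure section:

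- The examiner who gives the WMTB-C, RPM and TMT is kept unaware of allocation at T4 and at any T0 cognitive test done after the envelope is opened. Where feasible, the same applies to any research-team member who collects T4 data.
- The examiner works from an ID only, takes no part in case discussion, and sees no individual arm data until the last T4 test is scored.
- Families are asked before testing not to mention which treatment the child received.
- Any unblinding is recorded, with its timing, so that it can be reported with the cognitive results.

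No added staff or visits are needed. The cost is some separation of roles within the research team, a short instruction to families, and a log. Masking will be partial because some children will disclose their arm, and the log will show how often. If the full protocol already provides for this, one sentence in the article is enough.
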